**Methods:**

A randomized controlled trial will be performed with 1:1 allocation, blinded assessments, and an intention-to-treat analysis. Altogether, 46 individuals with PD, aged ≥50 years, who have bradykinesia and a sedentary or insufficiently active lifestyle, will be included. Participants will be randomly assigned to either (1) an experimental group (high-speed bodyweight resistance training) or (2) a control group (bodyweight intervention; usual speed). Both groups will perform a home-based, remotely supervised intervention, consisting of 60-minute individual sessions, 3 times per week over 12 weeks, with a trained physiotherapist. The primary outcome is bradykinesia of the lower limbs. The secondary outcomes are mobility, muscle power, dynamic balance, and quality of life. The effects of the training will be analyzed from the collected data by using the intention-to-treat analysis. Between-group differences will be measured by 2-way repeated measures ANOVA, considering the baseline, posttraining follow-up (primary time point), and 4-week follow-up (secondary time point).

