### Randomization

The randomization sequence will be computer-generated using a simple randomization method, in which each participant has an equal probability of being assigned to the experimental or control group. The sequence will be prepared prior to the start of the study by a trained research assistant who will not be involved in the study. The allocation will be maintained in sequentially numbered, sealed, opaque envelopes and stored in a locked cabinet and will not be accessible to investigators responsible for recruitment and assessment. After completion of the baseline assessment, the training therapist will open the next envelope in sequence to reveal the group allocation. Eligible participants will be randomly allocated to either the experimental or control group.

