### Primary Outcome Measure

Bradykinesia of the lower limbs will be measured using item 3.8 (leg agility), assessed bilaterally (right and left), and item 3.14 (global spontaneity of movement–body bradykinesia) of the motor examination of the MDS-UPDRS [25]. Each score ranges from 0 to 4, with 0 indicating normal function and 4 indicating severe impairment [25]. The primary bradykinesia outcome will be calculated as the sum of the bilateral scores for item 3.8 and the score for item 3.14, resulting in a composite score ranging from 0 to 12. Higher scores indicate more severe bradykinesia [28].

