### Sample Size

The sample size calculation was performed considering the primary outcome measure, bradykinesia (assessed using items 3.8, 3.9, 3.10, and 3.14 of the motor examination of the MDS-UPDRS) [25] based on data provided by a previous similar randomized controlled trial. The effect size for bradykinesia was derived from the study of Ni et al [11]. On the basis of a previous study [11] reporting a mean difference of –2.3 (SD 2.5), a sample size of 40 participants was required to achieve a power of 0.80 at a 2-tailed significance level (α=.05). Assuming a dropout rate of 15%, 46 participants will be recruited (23 per group).

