### Statistical Analyses

All statistical analyses will be performed by an independent examiner blinded to group allocation using SPSS for Windows (IBM Corp). Baseline characteristics will be summarized by treatment group using descriptive statistics. Means (SD) or median (IQR) will be used for continuous variables according to analysis of normality (Shapiro-Wilk test). Frequency (percentage) will be used for categorical variables.

All analyses will follow the intention-to-treat principle, including all randomized participants in the groups to which they were originally allocated. The primary outcome will be the lower limb bradykinesia score, with the primary end point defined as the postintervention assessment at 12 weeks. Analytic approaches will be used to handle missing data, as recommended by Jakobsen et al [37]. The specific procedure will depend on the proportion of missing data, as stated by Jakobsen et al [37]. The statistical models will include a random intercept for participants and fixed effects for time (before intervention, after intervention, and follow-up), group (intervention and control), and group-by-time interaction. The primary analysis will focus on the group-by-time interaction effect. The level of significance will be set at 5%. Effect estimates will be reported considering the CIs (95% CI) for the between-group mean differences at each time point (week 12 minus week 0 and week 16 minus week 0). Secondary outcomes will be considered exploratory. Where applicable, adjustment for multiple comparisons will be performed using the Bonferroni method [38].

Adverse events will be summarized descriptively by treatment group, including the number and proportion of participants experiencing at least one event, as well as the frequency and severity of events.

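### The primary contrast is an unadjusted difference in change from week 0; it is valid, but less precise than a baseline-adjusted estimate, and it over-corrects chance baseline imbalance

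*Protocol article*

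**What the plan says.** The Statistical Analyses section specifies a random intercept per participant and "fixed effects for time (before intervention, after intervention, and follow-up), group (intervention and control), and group-by-time interaction". It continues: "The primary analysis will focus on the group-by-time interaction effect". Effects are to be given with 95% CIs as "between-group mean differences at each time point (week 12 minus week 0 and week 16 minus week 0". Among the listed terms there is no baseline covariate and no constraint that the arms share a baseline mean.

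The abstract handles baseline in the same way, as a level of the time factor: "Between-group differences will be measured by 2-way repeated measures ANOVA, considering the baseline, posttraining follow-up (primary time point".

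The outcome is the sum of three item scores, "resulting in a composite score ranging from 0 to 12" (Primary Outcome Measure). The Sample Size section uses a previous trial "reporting a mean difference of –2.3 (SD 2.5", and does not say whether that SD belongs to a change or to a single assessment.

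**The concern.** Randomisation makes the expected baseline means equal, so a baseline difference between the arms is chance. A model with a free group effect at week 0 estimates that difference and carries its noise into the week-12 contrast. A change score also gives the baseline value a weight of exactly 1, whereas the weight that minimises variance is rho when the variances at the two visits are equal. Whenever rho is below 1, an arm that happens to start worse is therefore credited with some regression to the mean.

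At stake is precision in a small trial whose recruitment is closed at 46 (Results section), together with some dependence of the estimate on which arm happened to start worse. Because the model terms and the contrasts are written out, this is a choice the article has made and not a detail left to an analysis plan.

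**Working it through.** **Inputs from the protocol article.** Difference 2.3, SD 2.5, two-sided alpha 0.05, power 0.80, 40 evaluable, 46 recruited at 23 per group (Sample Size).

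**Assumed inputs.** Rho is not given, so 0.3 to 0.9 is used. Variances at baseline and week 12 are taken as equal.

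**1. The plan's own figure.** A two-sample t test with difference 2.3 and SD 2.5 has power 0.788 at 19 per arm and 0.809 at 20 per arm. The stated 40 is reproduced.

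**2. What the stated model estimates.** With complete data, the week-12 component of the interaction equals the difference in mean change. In a simulated data set with 23 per arm and rho 0.6, the mixed-model interaction and the raw difference in mean change were both -2.506. The standard error was 0.55, against 0.44 for analysis of covariance at week 12 and 0.50 for the mixed model with a common baseline mean. This is one illustrative data set. The general result is the next step.

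**3. Variance ratio.** Let s be the SD at one visit and k = 1/n1 + 1/n2.

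- Difference in change: 2 s²(1 - rho) k
- Baseline-adjusted difference: s²(1 - rho²) k
- Ratio, adjusted to change: (1 + rho)/2

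**4. Power at 20 per arm, taking 2.5 as the SD of change.** The adjusted analysis uses an SD of 2.5 × sqrt((1 + rho)/2) and loses one degree of freedom.

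| rho (assumed) | Variance ratio | Reduction in SE | Power, change score | Power, adjusted |
|---|---|---|---|---|
| 0.3 | 0.65 | 19% | 0.81 | 0.94 |
| 0.5 | 0.75 | 13% | 0.81 | 0.91 |
| 0.7 | 0.85 | 8% | 0.81 | 0.87 |
| 0.9 | 0.95 | 2.5% | 0.81 | 0.83 |

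**5. The same, taking 2.5 as the SD at a single assessment.** The change-score SD is then 2.5 × sqrt(2(1 - rho)) and the adjusted SD is 2.5 × sqrt(1 - rho²). Power goes from 0.67 to 0.84 at rho 0.3, from 0.81 to 0.91 at rho 0.5, and from 0.96 to 0.98 at rho 0.7.

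**6. Over-correction of a chance imbalance.** Given an observed baseline difference D, the change-score contrast is displaced by (1 - rho) × D in favour of the arm that starts worse. If 2.5 is the baseline SD, D has standard error 2.5 × sqrt(2/23) = 0.74 points. For an imbalance of one standard error the displacement is:

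- rho 0.3: 0.52 points, 22% of the target difference of 2.3
- rho 0.5: 0.37 points, 16%
- rho 0.7: 0.22 points, 10%
- rho 0.9: 0.07 points, 3%

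**The case against.** The model is a conventional one and nothing in it is invalid. It is unbiased over repeated randomisation and the type I error holds. That stands, and it limits the point to efficiency and conditional bias.

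The size depends on a rho that the document does not give, and at 0.9 the gain is slight. That stands too. The power figures also carry the planned effect over unchanged, although the Sample Size section derives it for a composite that includes items 3.9 and 3.10, which the primary outcome leaves out. They show the relative gain and are not a forecast of this trial's power.

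A reader might infer two stronger points that the document does not support.

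- **That chance imbalance goes uncorrected.** The contrast subtracts the baseline difference in full, so the fault is over-correction. For rho above 0.5 it still leaves less conditional bias than comparing week 12 alone: at rho 0.7 and an imbalance of one standard error, 0.22 points against 0.52.
- **That the allocation method makes this much worse.** The sequence is "computer-generated using a simple randomization method", but the chance of a baseline difference of at least 0.3 SD is about 0.31 with exactly 23 per arm, where the SD of the difference is sqrt(2/23) = 0.295. It is about 0.32 at a 19/27 split, where that SD is sqrt(1/19 + 1/27) = 0.299. Unequal arm sizes add almost nothing.

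Finally, changing a published primary analysis during follow-up has a cost in transparency. That is fair, and a dated amendment before unblinding meets it.

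**Conclusion.** The point holds as a loss of precision that can be avoided, not as an error that invalidates the trial. The stated primary contrast has 2/(1 + rho) times the variance of a baseline-adjusted one: 1.54 times at rho 0.3, 1.33 at 0.5 and 1.05 at 0.9. The gain from adjusting is material at low to moderate rho and small at high rho. Apart from one degree of freedom in the covariate version, adjustment costs no precision.

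The variance ratio rests on equal variances at the two visits and on complete data. The absolute power figures rest further on how SD 2.5 is read and on taking the planned effect at face value. The conditional displacement can go either way and averages to zero over randomisations.

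**What to change.** Before unblinding, and in a dated amendment, choose one of these as the primary model:

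- **Common baseline mean.** Keep week 0 as an outcome, drop the group main effect, and retain time, group × week 12 and group × week 16.
- **Baseline as covariate.** Model weeks 12 and 16 as outcomes, with the baseline 0-12 score as a covariate.

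The two give close but not identical results, particularly when data are missing, so one must be named in advance. Report the adjusted week-12 difference with its 95% CI as the primary estimate, and align the abstract's description of the analysis with it.

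The cost is a documented change to the published analysis model and, for the covariate version, one degree of freedom. The baseline score is already collected. The Results section says that the data have not yet been analysed, and the analyst is to be blinded to allocation, so the change can still be made cleanly.

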### Ethical Considerations

This trial received approval from the institutional ethics review board (Comitê de Ética em Pesquisa, Universidade Federal de Minas Gerais, *Certificado de Apresentação para Apreciação Ética* —CAAE: 68350023.7.0000.5149, number 6.016.310, April 23, 2023). All participants will provide written informed consent.

All data collected during in-person assessments and remote supervision sessions, including exercise adherence records, blood pressure and heart rate logs, and reports of adverse events, will be recorded using standardized forms and entered into electronic databases. These data will be stored in a password-protected cloud-based platform linked to a dedicated project email account. Access to the database will be restricted to authorized members of the research team through individual log-in credentials and permission-controlled folders. Identifiable information will be stored separately from coded research data to ensure confidentiality. Data will be retained in accordance with institutional and national regulations.

After publication of the primary and secondary results, the anonymized dataset underlying the findings will be made available upon reasonable request to the corresponding author, in accordance with institutional ethics approval and applicable data protection regulations.

## Results

Recruitment began in October 2024 and concluded in October 2025. A total of 46 participants were enrolled in the study. Data collection is currently in the follow-up phase. Upon completion of follow-up assessments, data collection will be finalized. Data analysis has not yet been performed. We anticipate that the results will be compiled and submitted for publication by May 2026.

## Discussion

This trial is designed to investigate whether remotely supervised home-based high-speed bodyweight resistance training can reduce bradykinesia and improve other outcomes, including mobility, muscle power, dynamic balance, and quality of life in individuals with PD. We hypothesize that participants undergoing the intervention will demonstrate greater improvements in these outcomes compared with the control group. If confirmed, these findings may support the feasibility and effectiveness of an accessible home-based intervention delivered through telerehabilitation that does not require specialized equipment and could reduce barriers to rehabilitation, thereby increasing its clinical applicability [13,39,40].

Previous studies have demonstrated positive effects of speed-based interventions on bradykinesia in individuals with PD [9-11], but have not specifically investigated home-based high-speed bodyweight resistance training, which has shown beneficial effects in older adults [14,15]. Because the intervention in this study will be delivered through telerehabilitation, it may contribute to expanding evidence-based practice and, consequently, improve the care of individuals with PD.

The trial incorporates methodological strengths such as randomized allocation, blinded assessment, and intention-to-treat analysis, which enhance the internal validity of the results. By focusing on movement speed, a key aspect of bradykinesia, this study may inform the development of targeted exercise strategies to improve functional outcomes in PD.

However, some limitations must be acknowledged. Due to the nature of the intervention, neither participants nor therapists can be blinded to group allocation, and caregiver supervision will be required during training sessions to ensure participant safety. Moreover, the findings of this trial will be generalizable primarily to Brazilian individuals with PD who share similar characteristics with the study sample. Therefore, caution is needed in extending the results to broader populations.

If the intervention proves effective, future studies may explore long-term adherence and implementation in different health care settings and geographic regions. Overall, this protocol may provide valuable evidence on a feasible intervention to reduce bradykinesia in individuals with PD, contributing to the development of accessible rehabilitation strategies.

The findings of this trial are expected to be disseminated through peer-reviewed publications and presentations at national and international scientific conferences, contributing to the advancement of accessible rehabilitation strategies for PD.

## Appendix

Multimedia Appendix 1 SPIRIT (Standard Protocol Items: Recommendations for Interventional Trials) checklist.

## Abbreviations

FTSTS: Five Time Sit to Stand
MDS-UPDRS: Movement Disorder Society–sponsored revision of Unified Parkinson’s Disease Rating Scale
Mini-BESTest: Mini-Balance Evaluation Systems Test
PD: Parkinson disease
PDQ-39: Parkinson’s Disease Questionnaire-39
SPIRIT: Standard Protocol Items: Recommendations for Interventional Trials
